### Sample size

Approximately 1’500 refugees reside in the initial intake facilities at the collaborating sites and could potentially participate. We estimate that approximately 30–50% will participate in the study over the years. Figure A.1 shows the power of our study with variations in sample size, effect size and predictors. It is important to note that our sample size will follow the naturalistic parallel group design of our study and thus may differ from the estimated sample size (See Fig. 3).

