## Statistical methods

### Statistical methods for primary and secondary outcomes

#### Feasibility assessment

[1a-d] Descriptive statistics (frequencies, percentages, means, standard deviations) will be used to assess the feasibility of NAT and the NAT counselling intervention programme in general (Table 4). These quantitative measures will be complemented by qualitative data from focus groups conducted with NAT counsellors as participants. The focus groups will explore perspectives on the need for the programme, areas for improvement, perceived effectiveness, barriers and facilitators to implementation, participants’ experiences and suggestions for improvement (Table 4). Content thematic analysis will be used to analyse the qualitative data to provide a comprehensive understanding of the feasibility and potential for improvement of the programme, using Nvivo software for data analysis.

**Table 4 Tab4:** Summarises the research questions and associated specific hypotheses

Research question	Alternative hypothesis	Null hypothesis	Ref.
Is the overall programme **sustainable**?	The majority ( > 50%) of refugees who leave the temporary accommodation have taken part in the project.	The minority ( < 50%) of refugees who leave the temporary accommodation have taken part in the project.	1a
	The programme is evaluated positively by stakeholders (refugees, counsellors, social workers).	The programme is evaluated negatively by stakeholders (refugees, counsellors, social workers) regarding issues that cannot be improved.	1b
	Recommendation to indicated treatment is followed by more than 50% of refugees.	Recommendation to indicated treatment is not followed by more than 50% of refugees.	1c
	The majority ( > 50%) of trained counsellor perform the screening and provide the intervention.	Only a minority ( < 50%) of trained counsellors perform the screening and provide the intervention.	1d
Is NAT **effective** (prevention)?	The number of participants with subclinical symptom levels at baseline who require specialised psychotherapeutic treatment after 6–9 months is lower in participants who received NAT than in the control group.	The number of participants with subclinical symptom levels at baseline who require specialised psychotherapeutic treatment after 6–9 months is equal in participants who receive the adapted NET compared to the control group.	2a

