	The number of participants with subclinical symptom levels at baseline who do not require treatment after 6–9 months is higher in participants who received NAT than in the control group.	The number of participants with subclinical symptom levels at baseline who do not require treatment after 6–9 months is equal in participants who receive the adapted NET compared to the control group.	2b
Is NAT **effective** (symptom reduction)?	Symptom reduction in participants with subclinical symptom levels is stronger in participants receiving NAT than in the control group (see Table 1).	Symptom reduction in participants with subclinical symptom levels is the same in participants receiving NAT compared to the control group (see Table 1).	3
[4] Is the programme generally cost-**effective**?	The financial costs of the NAT counselling intervention are lower than those of other interventions.	The financial cost of the NAT counselling intervention is equal to or higher than other interventions.	4

[2a+b] Chi-squared tests will be used to compare the frequency of participants with subclinical symptom levels requiring more/less intensive treatment during the programme. Logistic regression analysis will be considered to estimate the odds of refugees with or without NAT requiring more/less intensive treatment (Table 4).

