[4] We will estimate the cost-effectiveness of the NAT counselling intervention programme, respectively (Table 4). To this end, we will use cost-effectiveness analysis (CEA) based on the findings of the described trial and rely on established techniques from development and health economics [186–189]. In the first step, we will calculate the costs the NAT counselling intervention programme (as well as supervision, training, etc). Next, we will take into account prevented costs for specialised treatment, levels of improvement at symptom and daily life functionality (e.g. employment), and disability adjusted life years (DALYs) [190–193]. For each of the two compared strategies, a cost-effectiveness ratio (CER) will be calculated (cost versus outcome) allowing for an incremental cost-effectiveness ratio (ICER) which then allows for comparison of the NAT counselling intervention programme versus TAU and decision of superiority. We hypothesize that the NAT counselling intervention programme presents with a higher cost-effectiveness than TAU.

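### Table 4 states the cost-effectiveness hypothesis on cost alone, against unnamed interventions, and contradicts the planned ICER analysis against an undefined TAU

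*Protocol article*

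**What the plan says.** The second objective of the protocol article is to estimate the cost-effectiveness of the programme. Two places say how this will be judged.

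- **Table 4, ref. 4.** The research question is "Is the programme generally cost-effective". The alternative hypothesis is "The financial costs of the NAT counselling intervention are lower than those of other interventions" and the null is "The financial cost of the NAT counselling intervention is equal to or higher than other interventions". Neither mentions an effect, and the other interventions are not named.
- **Statistical methods, paragraph [4].** Programme costs are to be calculated. Avoided specialist treatment, improvement in symptoms and functioning, and DALYs are then taken into account. For each strategy "a cost-effectiveness ratio (CER) will be calculated (cost versus outcome) allowing for an incremental cost-effectiveness ratio (ICER"), which is to support "comparison of the NAT counselling intervention programme versus TAU and decision of superiority". The paragraph closes: "We hypothesize that the NAT counselling intervention programme presents with a higher cost-effectiveness than TAU". It says that the analysis rests on the results of this trial, using established health-economic methods.

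Table 1 lists the comparators that the study will have: people awaiting NAT, people waiting for or receiving psychotherapy, people under watchful waiting, and the same people before and after NAT. TAU is not among them. The term appears only in paragraph [4] and is not defined there or in the abbreviations.

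**The concern.** A cost-effectiveness claim needs both a cost difference and an effect difference. Row 4 has only the first. Taken as written, it accepts a cheaper programme that works less well and rejects a dearer one that works sufficiently better. Paragraph [4] uses the right ingredients, but with another hypothesis and another comparator, and nothing says which of the two governs.

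The comparator matters as well. Everyone in the study enters through the programme's screening step, so no observed group shows what happens without the programme. The article's Discussion expects the study to inform policy by demonstrating cost-effectiveness. A reader needs to know which rule produced that conclusion and which part of it was observed.

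**Working it through.** **Inputs.** The documents give no cost, effect or willingness-to-pay figures, so there is no plan figure to reproduce. The cost and effect pairs below are assumptions, in arbitrary units, chosen only to show when the two rules part.

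**Formulas.** Let ΔC and ΔE be the programme's cost and effect minus the comparator's, and λ the value placed on one unit of effect.

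- Row 4 accepts if ΔC < 0.
- CER = cost / effect for each strategy; ICER = ΔC / ΔE.
- Net benefit accepts if λ × ΔE − ΔC > 0.

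With λ = 0 the net-benefit rule becomes ΔC < 0, which is row 4. So row 4 gives the verdict of a decision maker who places no value on health gain.

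**Three assumed cases**, each against a comparator costing 1,000 for effect 0.05 (CER 1,000 / 0.05 = 20,000):

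| Case | Programme cost, effect | ΔC | ΔE | Programme CER | ICER | Row 4 | Net benefit accepts if |
|---|---|---|---|---|---|---|---|
| Dearer, better | 1,200, 0.10 | +200 | +0.05 | 12,000 | 4,000 | rejects | λ > 4,000 |
| Cheaper, worse | 900, 0.02 | −100 | −0.03 | 45,000 | 3,333 | accepts | λ < 3,333 |
| Cheaper, better | 900, 0.10 | −100 | +0.05 | 9,000 | −2,000 | accepts | any λ ≥ 0 |

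On the CERs, row 4 gives the opposite verdict in the first two cases and the same verdict in the third. On net benefit it is wrong in the first case for every λ above 4,000 and in the second for every λ above 3,333. The rules part only when cost and effect differ in the same direction. When one strategy is both cheaper and better, they agree.

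The first two ICERs are both positive but mean opposite things: 4,000 paid per unit gained, and 3,333 saved per unit lost. A hypothesis stated as a bare ICER would need the direction of the effect as well.

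**Comparator.** Row 4 compares with unnamed other interventions, and paragraph [4] with TAU. Under Eligibility criteria, every eligible person is offered the screening interview with feedback and referral. All Table 1 groups arise after that step. The psychotherapy groups are people scoring 37 or more whom the programme itself refers, so they are one of its steps and not a stand-in for its absence. Counting avoided specialist costs also needs a no-programme counterfactual, which no Table 1 group supplies.

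**The case against.** The strongest reply is that Table 4 is a summary and the method is in paragraph [4], which plans a proper analysis with costs, outcomes, DALYs and an ICER, and ties the superiority decision to it. That stands against a reading that a reader might infer: that the plan as a whole judges cost-effectiveness on cost alone. It does not. It does not remove the contradiction, because Table 4 is where the null and alternative hypotheses are written, and they differ from paragraph [4] in both criterion and comparator.

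A second reply is that nothing calls TAU a study arm, that health-economic methods can include a modelled comparator, and that referred clients are treated by ordinary German providers. This also stands in part. A reader might infer that the plan claims a TAU arm which it lacks, but the documents make no such claim. What remains is that TAU has no definition or stated source while the analysis is said to rest on the trial's findings. A willingness-to-pay value and the method for intervals may properly sit in the analysis plan, and their absence here is not part of this point.

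Third, the Limitations section already mentions the difficulty of comparing an intervention with a programme. It names the difficulty but does not say which comparison the cost-effectiveness claim will use.

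**Conclusion.** The point holds as an internal contradiction. Objective 2 has two stated criteria and two comparators. The row 4 criterion does not answer its own question, and it can mislead whenever the programme is dearer and better, or cheaper and worse. How likely that is cannot be computed, because the documents give no costs or effects; the thresholds of 4,000 and 3,333 belong to the assumed examples only. It would go too far to say that row 4 can never give the right verdict, since it does so when one strategy dominates. The TAU comparison is undefined and is not observed in any Table 1 group.

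One remark on the same table, not a defect. Row 1a asks that "The majority ( > 50%) of refugees who leave the temporary accommodation have taken part in the project", while the Sample size section expects that "approximately 30–50% will participate in the study over the years". On about 1,500 residents the forecast is 0.30 × 1,500 = 450 to 0.50 × 1,500 = 750, and more than half needs 751. A reader might infer that 1a is invalid or cannot be met. The documents do not support that. The rule returns a correct no or yes at whatever uptake occurs. With 1,500 independent persons, the chance of reaching 751 is about 0.00005 at 45% uptake, 0.06 at 48% and 0.49 at 50%. The bases may also differ: residents joining the study in one place, leavers who took part in the project in the other. The threshold need not be lowered.

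**What to change.** 1. Restate both hypotheses of Table 4, ref. 4 as a joint statement on cost and effect that matches paragraph [4], with one named comparator. An ICER below a stated threshold would serve where the programme is more effective. Incremental net benefit above zero at that threshold says the same and also covers the other directions.
2. Define TAU and say where its costs and outcomes come from.
3. Present programme versus TAU as a decision model with external inputs, not as a trial result.
4. Limit trial-based cost-effectiveness statements to contrasts that the study observes, such as NAT against awaiting NAT or against watchful waiting. Say that these concern NAT and not the whole programme, so they do not by themselves answer Objective 2.
5. Optionally, add a sentence beside row 1a noting the 30–50% forecast and whether both percentages use the same denominator.

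The cost is one rewritten table row and a few sentences in paragraph [4], best done before outcome data are analysed. The price is a more modest trial-based claim, because the programme-level conclusion will openly depend on modelled inputs.

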## Interventions

### Explanation for the choice of comparators

In this naturalistic study, the following potential comparators to NAT (treatment condition) evolve: (1) NAT clients awaiting treatment; (2) clients with clinically relevant symptoms who are either (2a) waiting for psychotherapy or (2b) receiving psychotherapy; (3) clients without symptoms waiting for follow-up; and (4) clients before vs. after NAT (individual trajectories of symptom development, Table 1).

**Table 1 Tab1:** Constellation of comparators

Treatment condition	Control condition	Limitation	Mitigation
[1] NAT	Awaiting NAT (RHS 13–36)	Reduced follow-up time points for those who wait for treatment; unknown N	-
[2] NAT	[2a] PT waiting [2b] PT receiving	Clients might still wait but may have started, or already finished PT; higher symptoms of the control group at baseline	Statistical control for the number of treatment sessions, use of the RDD
[3] NAT	Watchful waiting (RHS < 13)	Lower symptoms of the control group at baseline, low symptom levels generally	Evaluate number of clients who present with improving vs. deteriorating symptoms rather than
[4] After NAT	Before NAT	Within subject comparison; potential confounding factors	-

Note: RHS-15 = 15 item Refugee Health Screener with a sum score indicating symptom severity; PT = Psychotherapeutic sessions provided by a licensed Psychotherapist. Threshold to clinical relevance is suggested for ≥37. Watchful waiting is indicated for clients with ≤12 points

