### Criteria for discontinuing or modifying allocated interventions

In the event of danger to self or others, deterioration of trauma reactions or signs of other (comorbid) psychological symptoms, the client will be re-assigned to the red group and receive psychotherapeutic service or treatment at an acute care facility within the German health system. Thereafter, treatment delivery will follow the principles of the red group in full extent.

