### Implementation

To assign participants according to the RDD principles, we will use the RHS-15 (items 1–13) as eligibility criteria with two critical thresholds at 13 and 36 (see Fig. 4) as foreseen in the stepped-care model of the *NAT counselling intervention*. The RDD then assumes that the allocation to the conditions is nearly random within the determined bandwidth (RHS sum scores just above or below the cutoffs) and potential factors that would manipulate treatment effect vary randomly across participants in both groups. The *fuzzy* versus the *sharp* design version takes into account real-world implementation settings recognizing that participants with RHS scores in the yellow range need to be assigned to the red group, for instance, in cases of suicidal ideation or other negative psychological developments that requires treatment by clinical psychologist.

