[3] To assess the effectiveness of NAT compared to the comparison groups (see Tables 1 and 4), we will combine the figures resulting from RDD with traditional approaches (GLM, clinical significance). In the RDD, we will calculate a local average treatment effect (LATE) of the intervention on primary (RHS-15) and secondary (LSNS, BRS, SWLS, SSS8) outcomes (see Table 1). To this end, we will firstly test whether the main criteria for a valid RDD are held. Using a graphical method (scatterplot), we will examine the relationship between the eligibility (RHS at baseline) and outcome (follow-up) variables. We expect the RHS score to be discontinuous at the cutoff values. In contrast, we do not expect to see discontinuities in relevant covariates at the cutoff, which would violate the assumptions of an RDD. Next, separate regression lines will be fit on both sides of a cutoff value using an ordinary least squares (OLS) regression as the starting point. Alternative functional forms will be tested with the goal of ensuring an unbiased estimation. The LATE will be computed directly as the difference between the regression lines at the cut-off (intercept). To test the statistical significance of the difference between the two conditions, we will use a *t*-statistic, dividing the treatment effect (difference between regression lines at cut-off) by the sum of the square of the standard errors of the comparison group (*SE*_*comparison*_) and the intervention group (*SE*_*interventio*n_). The calculated *t*-statistic will then be compared to a critical value from the *t*-distribution for the given degrees of freedom (*DF*). The degrees of freedom will be determined based on the number of the observations and the parameters estimated in the two separate regressions. In the most simple form, *DF = n*_*comparison*_
*+ n*_*intervention*_
*- 4*. The test will be two-sided. Moreover, we will run falsification tests and sensitivity analysis to ascertain the validity of the RDD [178], examine whether results are sensitive to the choice of bandwidth [144], run placebo tests on exogenous covariates and on the outcome at values other than the actual cutoffs [145]. Prespecified subgroup analyses will explore potential heterogeneity in treatment effects across different demographic and clinical characteristics. Adjusted analyses will account for potential confounding factors identified a priori.

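### Hypotheses 2a/2b compare clients by NAT received, with an unadjusted chi-squared test and no rule for clients re-assigned to red before NAT starts, so the test is open to immortal-time and selection bias

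*Protocol article*

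**What the plan says.** All references are to the protocol article.

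- **Grouping.** Table 4, ref. 2a, predicts that the number of initially subclinical participants needing specialised treatment at 6–9 months "is lower in participants who received NAT than in the control group". Ref. 2b uses the same grouping for those needing no treatment.
- **Test.** Under [2a+b]: "Chi-squared tests will be used to compare the frequency of participants with subclinical symptom levels requiring more/less intensive treatment during the programme". The next sentence adds: "Logistic regression analysis will be considered to estimate the odds of refugees with or without NAT requiring more/less intensive treatment". No covariates, time origin or classification rule are given there.
- **Control.** Table 1, row 1, gives the control for subclinical clients as those awaiting NAT (RHS 13–36). Its stated limitation is "Reduced follow-up time points for those who wait for treatment; unknown N", and the mitigation cell holds only a dash.
- **Re-assignment.** Under the criteria for discontinuing or modifying allocated interventions, in the event of "deterioration of trauma reactions or signs of other (comorbid) psychological symptoms, the client will be re-assigned to the red group". The Implementation section also expects that "participants with RHS scores in the yellow range need to be assigned to the red group", and handles this through the fuzzy version of the regression discontinuity design (RDD).
- **Adjustment.** "Adjusted analyses will account for potential confounding factors identified a priori" stands under [3], the symptom-reduction analysis, not under [2a+b].
- **Non-adherence.** The section on non-adherence and missing data selects participants by completeness of baseline data. It does not say in which group a re-assigned client is analysed.

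**The concern.** Both hypotheses are limited to clients in the yellow range at baseline, so the contrast is between yellow clients with and without NAT. That status is settled during follow-up, and the event can block it: a client who turns red before the first session no longer gets NAT. Turning red is also close to the 2a outcome itself, the need for specialised treatment. The time between eligibility and NAT start is therefore event-free by construction for NAT recipients and at risk for everyone else. That is immortal-time bias.

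Uptake may also depend on severity, and a chi-squared test cannot adjust for baseline RHS. The RDD and the adjusted analyses are planned for [3], so they do not repair 2a/2b. At stake is the claim that NAT prevents escalation to specialised care.

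The outcome is also worded in two ways. Table 4 reads need for treatment at 6–9 months, while the test sentence reads it over the course of the programme. The size of the bias depends strongly on which is meant.

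**Working it through.** **Inputs.** The article gives no event rate, waiting time, uptake or group size for 2a/2b, so there is no figure of its own to reproduce. All of the following are assumed: NAT has no effect; deterioration to red has a constant hazard h = 0.03 per month; follow-up is T = 7.5 months (the middle of 6–9); the wait is uniform on 0 to W months; acceptance is a = 60% or 80%; there are 250 yellow clients; the chi-squared test is two-sided at 5%.

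**Step 1. True risk, the same for everyone.** 1 − exp(−0.03 × 7.5) = 1 − 0.7985 = 20.15%.

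**Step 2. Clients re-assigned before NAT counted as controls, outcome ever red.** Let E = (1 − exp(−hW))/(hW) be the chance of reaching the end of the wait without turning red. Then:

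- share receiving NAT = aE
- share receiving NAT and later red = a(E − 0.7985)
- control risk = [0.2015 − a(E − 0.7985)] / (1 − aE)

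*W = 3, a = 0.6:* E = 0.9563. NAT risk = 0.0947/0.5738 = 16.5%. Control risk = (0.2015 − 0.0947)/0.4262 = 25.1%. Relative risk = 0.66.

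*W = 6, a = 0.8:* E = 0.9152. NAT risk = 0.0933/0.7321 = 12.7%. Control risk = (0.2015 − 0.0933)/0.2679 = 40.4%. Relative risk = 0.32.

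Both relative risks would be 1 if the comparison were unbiased.

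**Step 3. Rejection rate of the chi-squared test, simulated, no NAT effect.**

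| Handling of clients re-assigned before NAT | Outcome | Wait | Rejection |
|---|---|---|---|
| Counted as controls | ever red | up to 1 month | about 6–17% |
| Counted as controls | ever red | up to 3–6 months | 40% to over 99% |
| Dropped | ever red | up to 3–6 months | 11–34% |
| Counted as controls | status at 6–9 months, recovery 0.3/month after referral | up to 3–6 months | 5–25% |
| Group fixed at baseline | ever red | any | about 5% |

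Dropping them does not remove the bias. With W = 3 the NAT risk stays at 16.5% while the control risk is the true 20.15%, because only the acceptors are filtered on staying well.

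**Step 4. A second model.** With exponential waits, 300 clients, 20% red risk and a mean wait of 2 months, the red proportions are 15.6% with NAT and 23.6% in control at 50% uptake (41% rejection), and 15.7% and 32.6% at 80% uptake (88%). With 150 clients, 10% risk, a mean wait of 0.5 month and 50% uptake, rejection is 5%, so there is no visible inflation. Fixing the group at baseline, with uptake unrelated to prognosis, gives 3–7% throughout.

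**Step 5. Selection by severity.** If sicker clients are much more likely to take up NAT and the mean wait is 0.25 month, red is 24.9% with NAT and 19.0% in control, with 23% rejection against NAT. At a mean wait of 1 month the two biases roughly cancel (6%). With this dependence, fixing the group at baseline without adjustment still rejects in 32–38% of null trials, so baseline RHS must also be in the model.

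**The case against.** The strongest reply is that the article never says a client who deteriorates while waiting is counted as a control. The re-assignment rule is not limited to waiting clients, so a client who worsens during NAT also goes red and can count against NAT. The Table 1 control is clients awaiting NAT, and a re-assigned client is arguably no longer waiting. This is correct: a reader might infer that the plan places these clients in the control group, but the text leaves their classification open. Two of the natural readings, counting them as controls or dropping them, are biased all the same. Later deterioration of NAT clients is already counted as NAT events in the figures above.

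A reader might also infer that a snapshot at 6–9 months favours NAT, because a NAT client who was re-assigned, treated and recovered then counts as a success. The same rule applies to controls. If early re-assignments concentrate among controls, those clients have had the longest time to recover, so the snapshot removes more control events and offsets the bias.

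Finally, 2a/2b are not the primary analysis: RHS-15 is, under [3]. The Limitations section concedes that randomisation is compromised and asks for cautious reading, and logistic regression is named. These points limit the weight of the issue. They do not repair it, because the grouping and the only committed test are stated for 2a/2b, and a general caveat gives the reader no corrected estimate.

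**Conclusion.** The point holds in this form. For 2a/2b the plan groups by a non-randomised, post-baseline exposure that the outcome can block, commits only to an unadjusted test, leaves clients re-assigned before NAT unclassified and words the outcome in two ways. The test is therefore open to immortal-time bias, which favours NAT when waits are non-trivial, and to selection by severity, which can go either way.

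The size cannot be fixed from the article. Under the assumptions above it runs from almost nothing (waits of a few weeks, or status read only at 6–9 months with recovery) to near-certain false rejection (waits up to 6 months, 80% acceptance, outcome ever red, counted as controls). The stronger claim, that the plan as written manufactures a NAT benefit, is not supported. It needs a classification rule that the article does not state, together with waiting times and uptake that it does not give.

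**What to change.** For 2a/2b:

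1. Set time zero at the date of eligibility for all yellow participants.
2. Choose one handling of exposure. One option is to fix the group at time zero, for example by offer, and keep re-assigned clients in it. Another is to define the group by NAT status at a landmark, count later events only, and keep clients re-assigned afterwards in their group. The third is to treat NAT start as a time-varying exposure. If every yellow client is offered NAT at once, grouping by offer gives no contrast and one of the other two is needed.
3. Make a regression adjusted for baseline RHS and site the committed analysis, with the chi-squared test as description only.
4. Reconcile the two outcome wordings, and report ever re-assigned or referred separately from status at 6–9 months.

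**Cost.** NAT start and re-assignment dates must be taken from programme records; the article does not say that they are kept. The apparent effect will be less favourable, or diluted where the group is fixed before NAT is received. A landmark discards early events. NAT clients are supervised more closely than waiting clients, so more re-assignments may be detected among them. An ever-re-assigned outcome can then work against NAT, which is a further reason to report both outcomes.

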## Assignment of interventions: allocation

Random allocation to treatment and control conditions is crucial in establishing causal inference. However, this approach is costly and raises ethical concerns when evidence-based treatment is existing and vulnerable populations are studied over extended periods. Therefore, the regression discontinuity design (RDD), introduced by Thistlethwaite and Campbell in the 1960s [141], serves as a powerful quasi-experimental alternative and has been applied in the field of counselling [142]. In brief, the RDD defines eligibility based on a *bandwidth* around a cutoff of a continuous variable that determines assignment. The premise underlying RDD is that participants near the cutoff are similar in all relevant respects except for treatment assignment, thus “as-if random” in this localized context. The *fuzzy* RDD also allows for deviation from the cutoff as criteria for single cases (systematic manipulation is however not allowed). With it, RDD provides an unbiased estimate of the local treatment effect, simulating a randomized controlled experiment for participants near the cutoff or within the bandwidth, respectively [141, 143–146].

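### The plan adopts a fuzzy regression discontinuity design but computes the LATE with the sharp-design estimator, so the reported jump is an intention-to-treat effect at the cutoff

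*Protocol article*

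**What the plan says.** **Design.** Under Assignment of interventions: allocation, the article explains that the fuzzy "RDD also allows for deviation from the cutoff as criteria for single cases". Under Implementation it sets two thresholds on the baseline RHS score, which separate 12 from 13 and 36 from 37. It says that the fuzzy rather than the sharp version "takes into account real-world implementation settings recognizing that participants with RHS scores in the yellow range need to be assigned to the red group". Criteria for discontinuing or modifying allocated interventions adds that, on danger, deterioration or other symptoms, "the client will be re-assigned to the red group and receive psychotherapeutic service".

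**Analysis.** In item [3] of Statistical methods for primary and secondary outcomes, the plan states that "we will calculate a local average treatment effect (LATE) of the intervention on primary (RHS-15" and on secondary outcomes. Separate OLS lines are fitted on the two sides of a cutoff, and "The LATE will be computed directly as the difference between the regression lines at the cut-off (intercept". The t-test has n(comparison) + n(intervention) − 4 degrees of freedom in its simplest form.

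**Hypothesis.** Hypothesis 3 in Table 4 is about symptom reduction among participants who receive NAT, compared with the control group.

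**The concern.** A fuzzy design has two jumps at the cutoff: one in the outcome and one in the probability of receiving the treatment. The effect of receipt, for those whose receipt depends on the side they fall on, is the ratio of the two. The plan uses the outcome jump alone and calls it the LATE of the intervention. That is correct only when receipt goes from nobody to everybody at the cutoff, which the plan says it does not expect.

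What is at stake is how the main RDD result on the primary outcome is read. A reader would take the figure as the effect of receiving NAT. It would actually be the effect of scoring on the NAT side, diluted by everyone on that side who did not receive NAT. The cost-effectiveness analysis, which builds on the trial's findings, could carry the same mislabelled figure forward.

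**Working it through.** **1. Is receipt modelled anywhere?** The lines in item [3] are fitted by side of the cutoff, and only to outcomes. The degrees of freedom subtract 4: two intercepts and two slopes. The article names no model for NAT receipt, no ratio estimator, no two-stage least squares and no instrument. The listed checks (functional form, bandwidth, placebo outcomes and cutoffs, falsification, covariate adjustment) do not rescale for non-receipt.

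**2. Inputs.** The protocol gives no numerical effect or receipt rate that could be reproduced here. The size of the receipt jump is therefore assumed, over a range of 0.5 to 1.0.

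**3. The 12/13 cutoff (watchful waiting on the other side).** Let p1 and p0 be the probabilities of receiving NAT just above and just below the cutoff. If crossing the cutoff acts only through NAT receipt, and never makes anyone less likely to receive it:

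- outcome jump = LATE × (p1 − p0)
- LATE = outcome jump ÷ (p1 − p0)

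Shrinkage of the raw jump is 1 − (p1 − p0). To put this on the RHS scale, a true effect of −4 points is assumed; this figure is illustrative and is not in the documents.

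| Receipt jump | Raw jump (formula) | Shrinkage | Raw jump (simulated) | Ratio (simulated) |
|---|---|---|---|---|
| 1.0 | −4 × 1.0 = −4.0 | 0% | −4.01 | −4.01 |
| 0.9 | −4 × 0.9 = −3.6 | 10% | −3.63 | −4.04 |
| 0.8 | −4 × 0.8 = −3.2 | 20% | −3.23 | −4.03 |
| 0.7 | −4 × 0.7 = −2.8 | 30% | −2.79 | −3.98 |
| 0.5 | −4 × 0.5 = −2.0 | 50% | −2.03 | −4.04 |

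The simulation used 2,000 runs of 600 participants, a cutoff between 12 and 13, and separate OLS lines on each side. When non-receipt was made to depend on an unmeasured predictor of the outcome, the results barely changed (at 0.5: −1.99 raw, −3.96 ratio).

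**4. The 36/37 cutoff (referral to psychotherapy on the other side).** Let a be the effect of NAT and b the effect of psychotherapy, each against neither and taken as constant for illustration. Let Δq and Δr be the differences in receipt of NAT and of psychotherapy, yellow side minus red side:

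- outcome jump = a·Δq + b·Δr

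If everyone follows the score, Δq = 1 and Δr = −1, and the jump is a − b: NAT against psychotherapy. If a share c of yellow-side clients moves to psychotherapy, the jump is (1 − c)(a − b). That shrinks the contrast and would flatter NAT if psychotherapy does better. If only a share q of the yellow side receives NAT, only a share r of the red side receives psychotherapy and the rest receive neither, the jump is a·q − b·r. This differs from a − b by b(1 − r) − a(1 − q), which can have either sign. Dividing by Δq gives a + b·Δr/Δq, which is not the effect of NAT against no NAT.

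**5. The null.** At 12/13 the jump is zero exactly when the ratio is zero, provided that receipt jumps at all. The test of no jump is therefore not changed by this point.

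**The case against.** The strongest reply is that the distortion may be small and that the plan does not rest on this figure alone. The article ties fuzziness to isolated cases. On that reading the receipt jump may be 0.9 or more, and shrinkage at 12/13 is at most 10%. The raw jump there is a legitimate intention-to-treat effect and is conservative for NAT. OLS is offered only as a starting point, Table 1 adds adjustment for the number of treatment sessions, and mixed models and clinically significant change accompany the RDD. All this limits severity, but it does not remove the inconsistency. The alternatives to OLS that the plan mentions change the shape of the lines, not the estimand. The session count is measured after assignment, so adjusting for it does not replace a model for receipt.

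Several stronger readings are tempting, but the documents do not support them:

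- **That the plan understates NAT throughout.** This holds cleanly only at 12/13. At 36/37 the direction is open (step 4 of the working).
- **That the effect is halved.** Hypothesis 1c ("Recommendation to indicated treatment is followed by more than 50% of refugees") is a sustainability criterion that covers all recommendations, including referrals of the red group. It is neither an expected NAT uptake nor a receipt jump.
- **That the waiting-list row of Table 1 shows large non-receipt.** Clients awaiting NAT are a separate, deliberate comparator within the yellow range. The stated limitation ("Reduced follow-up time points for those who wait for treatment; unknown N") fixes no receipt rate.
- **That clients who wait, decline or are re-assigned will be dropped.** The lines are fitted by score, the missing-data section includes all eligible participants with adequate baseline data, and the retention section seeks outcomes from those who deviate.

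**Conclusion.** The estimator stated in item [3] contradicts the design adopted under Implementation. This is not a detail left to an analysis plan, because the article fixes the formula. What is wrong is the label, the effect size as an answer to hypothesis 3, and the interval read as one for the effect of receipt. The test of no jump stands.

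At 12/13 the shrinkage equals one minus the receipt jump: 10% to 50% over an assumed range of 0.9 to 0.5, and little if crossover is rare. This rests on crossing the cutoff never lowering NAT receipt and acting on the outcome only through NAT receipt. The second condition is plausible in part because Table 2 refers clients in acute danger to specialist care whatever their score, but it remains an assumption. At 36/37 neither the size nor the direction can be stated. Severity: should be fixed.

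**What to change.** Amend item [3] of the statistical methods:

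1. **Both cutoffs.** Label the raw jump as the intention-to-treat effect at that cutoff. State that every participant stays on the side given by the baseline score, whatever was received.
2. **12/13.** Estimate the LATE as the outcome jump divided by the jump in NAT receipt, by local two-stage least squares with separate slopes and the same bandwidth. Define receipt in advance, report the receipt jump, and give a matching or weak-instrument-robust confidence interval.
3. **36/37.** Define the contrast as NAT versus the psychotherapy pathway and report receipt of each treatment by side. Do not present a two-stage ratio there as the effect of NAT versus no NAT.

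The cost is some wording and a short piece of code. The per-session, per-client adherence forms described under Assessment (NAT counsellors) already document receipt of NAT; psychotherapy receipt is needed in any case for the session adjustment in Table 1. The price is a wider interval for the LATE. Ignoring uncertainty in the receipt jump, it is 1 ÷ 0.9 = 1.11, 1 ÷ 0.7 = 1.43 or 1 ÷ 0.5 = 2.0 times as wide as that of the raw jump.
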